#### Participants

Typically developed participants will be recruited from a public announcement posted on Tecnologico de Monterrey, Campus Monterrey. ASD participants will be recruited by contacting parents of autistic children attending San Jose Hospital from Tecnologico de Monterrey.

##### Social Stories^TM^ and robot utterances recordings

Participants will be healthy TD volunteers. Adults will be aged 19–35 and children will be aged 9–11 years old. One participant for each type of voice will be included (e.g., one adult male). The same inclusion and exclusion criteria than the one described in Stage 1 will be followed.

##### Validation of Social Stories^TM^

Sample size estimation was calculated with G^∗^Power software version 3.1.9.7 (Faul et al., 2007) for Cohen’s d effect size index of 0.8, statistical significance set at *p* < 0.05. Results indicated that 34 participants would be enough to provide an estimated power of 0.90. Therefore, 40 healthy TD aged between 9 and 11 years old will volunteer. Participants will be excluded if they have a clinical history of any pathology that affects emotional behavior, hearing, or speech at the time of the study.

##### Intervention

Autistic and TD participants involved in this study will have to meet the same criteria than those described in Stage 2. However, participants from Stage 2 will not be included in Stage 3 in order to avoid any bias elicited by a former exposition to the synthetic voices under study.

Sample size estimation was calculated with G^∗^Power software version 3.1.9.7 (Faul et al., 2007) for Cohen’s d effect size index of 0.8, correlations among repeated measures of 0.5, and statistical significance set at *p* < 0.05. For ERP analysis, results indicated that 13 participants in each group would be enough to provide an estimated power of 0.92 for group comparisons, and 11 participants in each group would be enough to provide an estimated power of 0.91 for assessment sessions comparisons. For behavioral analysis on reaction times, results indicated that 13 participants in each group would be enough to provide an estimated power of 0.91 and seven participants in each group would be enough to provide an estimated power of 0.93 for assessment sessions comparisons. For behavioral analysis on number of correct/incorrect answers, results indicated that 18 participants in each group would be enough to provide an estimated power of 0.92 for group comparisons, and 15 participants in each group would be enough to provide an estimated power of 0.90 for assessment sessions comparisons (Cohen’s d effect size index of 0.8, statistical significance set at *p* < 0.05). For behavioral analysis on ASRS scores, results indicated that 16 participants in each group would be enough to provide an estimated power of 0.92 and 18 participants in each group would be enough to provide an estimated power of 0.90 for assessment sessions comparisons.

A total of 72 participants will take part to this Stage and will be divided in four groups:

•Group 1: autistic children receiving robot, synthesized and human voices intervention (18 participants).•Group 2: autistic children receiving robot and human voice intervention (18 participants).•Group 3: autistic children without receiving intervention (18 participants).•Group 4: TD children without receiving intervention (18 participants).

Group 1 will be the experimental group and groups 2–4 will be controls. Children from group 2 will receive the same intervention as children from group 1, with the exception of the use of human voices only. This group will help to evaluate the efficacy of the use of synthesized voices in the intervention. Autistic participants will be randomly assigned to any of groups 1, 2 or 3. All four groups will be included in pre-, mid-, end and follow-up assessments.

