##### Statistical analysis on ERPs data

The statistical significance of ERP components will be tested by comparing their mean amplitudes to zero at ROIs using one-sample *t*-tests. This method will allow us to focus exclusively on significant responses, and to distinguish significant scalp distributions from noise. Statistically significant ERPs will be considered for further amplitude analysis.

Group comparisons will be conducted by Group × ROI repeated measures ANOVAs on each ERP and assessment session separately, for standard stimuli. Similarly, for deviant stimuli, Group × ROI × Deviant repeated measures ANOVAs will be performed.

For standard stimuli, time comparisons will be conducted by Assessment Session × ROI repeated measures ANOVAs on each ERP and group separately. For deviant stimuli, Assessment Session × ROI × Deviant repeated measures ANOVAs will be performed.

Scalp distribution comparisons for standard stimuli will be assessed by Group × Laterality (FP1, F3, F7, T7, C3, P3, P7, O1/AFz, Fz, CPz, Cz, POz, Pz/FP2, F4, F8, T8, C4, P4, P8, O2) repeated measures ANOVAs on each ERP and assessment session separately. For deviant stimuli, Group × Laterality × Deviant repeated measures ANOVAs will be conducted.

For all amplitude analysis, normality will be assessed by Shapiro–Wilk test. In case of non-parametric distribution of the data, a transformation will be applied. Mauchly’s test of sphericity will be used to evaluate homogeneity of variances and co-variances. In case of violation of sphericity, a Greenhouse-Geisser correction will be applied in order to test main effects significance. *Post hoc* comparisons will be conducted to assess specific differences (Tukey procedure).

All statistical analysis will be performed with R software. Level of significance will be set at *p* < 0.05.

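### Stage 3 states group-comparison power but none for Group 1 versus Group 2, the pair that isolates the synthesized voice; at 18 per group and d = 0.8 that pair has power 0.41 to 0.77 under Tukey

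*Protocol article*

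**What the plan says.** All references are to Stage 3 of the protocol article.

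- **Design.** Participants, Intervention: "A total of 72 participants will take part to this Stage and will be divided in four groups", 18 in each. Groups 1 to 3 are autistic children assigned at random: robot with synthesized and human voices, robot with human voice only, and no intervention. Group 4 is TD children without intervention.
- **Purpose of Group 2.** It receives the same intervention as Group 1 except that only human voices are used, and "This group will help to evaluate the efficacy of the use of synthesized voices in the intervention". The Conclusion gives testing the efficacy of less-natural voices as the aim of this stage.
- **Power inputs.** Cohen's d "effect size index of 0.8, correlations among repeated measures of 0.5, and statistical significance set at" 0.05.
- **Stated group powers.** ERPs: "For ERP analysis, results indicated that 13 participants in each group would be enough to provide an estimated power of 0.92 for group comparisons". Reaction times: "For behavioral analysis on reaction times, results indicated that 13 participants in each group would be enough to provide an estimated power of 0.91". Correct answers: "18 participants in each group would be enough to provide an estimated power of 0.92 for group comparisons". ASRS: "For behavioral analysis on ASRS scores, results indicated that 16 participants in each group would be enough to provide an estimated power of 0.92". The reaction-time and ASRS sentences do not say which comparison the first figure is for. I read it as the group comparison because the second figure in each is labelled as the session comparison.
- **Planned tests.** For ERPs, "Group comparisons will be conducted by Group × ROI repeated measures ANOVAs on each ERP and assessment session separately" for standard stimuli, with Deviant added as a factor for deviant stimuli. Reaction times use Group × Stimulus (six stimuli). ASRS and correct answers use one-way ANOVAs. Pairwise differences come only post hoc: Tukey for ERPs and reaction times; Tukey, or Holm-adjusted Wilcoxon after Kruskal–Wallis, for ASRS and correct answers.

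**The concern.** An omnibus F across four groups asks whether any of them differ. With TD children among the four, it can be significant because TD and autistic children differ, which the Discussion leads one to expect, while the two robot groups are identical. Three equal autistic groups and a TD group about 0.92 SD away already give f = 0.4, the effect size behind the ERP calculation. Power for that test says little about power to separate Group 1 from Group 2.

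A non-significant Group 1 versus Group 2 result could be taken to show that synthesized voices add nothing, on the strength of stated powers of 0.91 to 0.92 that do not apply to that pair.

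**Working it through.** **Inputs.** d = 0.8, so f = d/2 = 0.4; correlation ρ = 0.5; α = 0.05; 18 per group planned; k = 4 groups. The Stage 2 Data Analysis section, which Stage 3 reuses, lists 18 regions of interest. With 5 deviants that makes m = 90 ERP measures. Reaction times have m = 6. ASRS and correct answers have m = 1.

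**Step 1. Reproduce the ERP figure.** For the Group effect in a repeated-measures ANOVA (between factors), with N = kn:

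λ = f²·N·m / (1 + (m − 1)ρ), df = k − 1 and N − k.

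For n = 13, k = 4, m = 90: λ = 0.16 × 52 × 90 / 45.5 = 16.46, with df 3 and 48. Power is **0.920**, as stated. With the same inputs, three groups give 0.864 and two groups 0.786.

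**Step 2. Try the other stated group powers as four-group omnibus tests at f = 0.4.**

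| Outcome | n per group | m | λ | Computed | Stated |
|---|---|---|---|---|---|
| ERPs | 13 | 90 | 16.46 | 0.920 | 0.92 |
| Reaction times | 13 | 6 | 14.26 | 0.875 | 0.91 |
| Correct answers | 18 | 1 | 11.52 | 0.80 | 0.92 |
| ASRS | 16 | 1 | 10.24 | 0.74 | 0.92 |

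Only the ERP figure reproduces. Reaction times reach 0.914 if m = 30 (6 stimuli × 5 sessions), but the protocol analyses each session separately, so m = 30 is an assumption. Correct answers would need f of about 0.47, and ASRS f = 0.50 (0.917). The document states neither value.

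**Step 3. Power for Group 1 versus Group 2 at d = 0.8.** The mean of m equally correlated measures has variance v = (1 + (m − 1)ρ)/m relative to one measure. The noncentrality is (d/√v)·√(n/2), with 4(n − 1) error df. The Tukey critical value is q(0.95; 4, df)/√2.

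At n = 18, df = 68. The Tukey critical value is 2.63 and the critical t for a single planned contrast is 2.00.

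| Outcome | v | Noncentrality | Tukey | One planned contrast |
|---|---|---|---|---|
| Single score (ASRS, correct answers) | 1 | 2.40 | **0.41** | 0.66 |
| Reaction times (m = 6) | 0.583 | 3.14 | **0.69** | 0.87 |
| ERPs (m = 90) | 0.506 | 3.38 | **0.77** | 0.91 |

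With only the two groups' own error df, the planned contrast gives 0.645, 0.863 and 0.906; hence about 0.65, 0.87 and 0.91. A simulation of 100,000 runs gave Tukey power of 0.414 (single score) and 0.767 (ERPs). Also requiring a significant omnibus F left these at 0.412 and 0.767.

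**Step 4. Like for like on ERPs.** At n = 13 the omnibus has 0.92 and the Tukey contrast 0.58. At n = 18 the omnibus has 0.98 and the Tukey contrast 0.77.

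**The case against.** **The omnibus explanation does not cover every figure.** This stands. A reader might infer that all four stated group powers are four-group omnibus powers and that each simply drops to 0.41–0.77 for the voice contrast. The document does not support that. The 0.92 for correct answers and for ASRS is not omnibus power at d = 0.8, so the gap from 0.92 to 0.41 mixes an unexplained effect size with the choice of comparison. The stated powers also belong to 13, 13, 18 and 16 per group, while 0.41–0.77 is for 18.

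**Eighteen exceeds the 13 required for ERPs.** This stands in part. As one planned contrast, Group 1 versus Group 2 on ERPs has about 0.91 at 18 per group. The ERP shortfall at 18 comes from the Tukey adjustment. Under the printed plan, though, the figure is 0.77.

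**Group 1 versus Group 2 is not the only question.** This stands. The protocol calls Groups 2 to 4 all controls, has an untreated autistic group, expects improvement over time, powers session comparisons separately and names no primary contrast. But it gives Group 2 precisely this purpose, and no other pair isolates the voice.

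**Tukey is not always the route.** ASRS and correct answers may go to Holm-adjusted Wilcoxon, for which I computed no power. The 0.41 applies to the Tukey route.

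**A full analysis plan may hold the contrast.** It may. The point rests on power figures and tests that the article itself prints, and on figures there that do not reproduce.

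**Conclusion.** The concern holds in a limited form. The stated Stage 3 group powers do not describe the comparison that judges the synthesized voice. The ERP figure is four-group omnibus power that includes TD children. The other three do not reproduce from d = 0.8 even on that reading: 0.80 and 0.74 against 0.92, and 0.875 against 0.91.

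Under Tukey at 18 per group and a true d of 0.8, Group 1 versus Group 2 would be missed in about 59% of trials on a single score, 31% on reaction times and 23% on ERPs. A planned contrast would cut these to about 35%, 13% and 9%.

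The reaction-time and ERP figures assume correlation 0.5 and the same d = 0.8 in every stimulus or ROI-by-deviant cell; an effect confined to some cells would give less. No withdrawals are allowed for, although the Discussion warns that the rate may be high. The effect size is the protocol's own and I have not judged whether it is realistic.

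**What to change.** In the Stage 3 Participants, Intervention section:

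1. Label the ERP figure (13 per group, 0.92) as power for the four-group omnibus test, TD group included.
2. Correct the correct-answers, ASRS and reaction-time figures, or state the effect size and number of measures that produce them. Do not label these three as omnibus power at d = 0.8.
3. State the power of Group 1 versus Group 2 at 18 per group for each outcome: as a planned contrast, about 0.65 for ASRS and correct answers, 0.87 for reaction times and 0.91 for ERPs, with the correlation and equal-effect assumptions.

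In the Stage 3 statistical analysis sections, prespecify Group 1 versus Group 2 as a planned contrast instead of one of six post hoc pairs. The other pairs can stay under the existing post hoc procedures.

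The cost is protocol wording and a less favourable stated power for the single-score outcomes. No extra participants are needed.

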#### Data Analysis

##### Statistical analysis on ASRS scores

Group comparisons will be conducted by one-way ANOVAs on T-scores for each assessment session and symptom domain (Social/Communication, DSM-IV-TR, Peer and Adult Socialization, and Social/Emotional Reciprocity) separately.

Time comparisons (between assessment sessions) will be tested by one-way ANOVAs on T-scores for each group and symptom domain (Social/Communication, DSM-IV-TR, Peer and Adult Socialization and Social/Emotional Reciprocity) separately.

Normality and homogeneity of variances will be assessed by Shapiro-Wilk and Bartlett tests, respectively. In case of non-parametric distribution of the data, Kruskal-Wallis test will be applied. Post-hoc comparisons will be conducted to assess specific differences (Tukey procedure in case of ANOVA, Wilcoxon tests with *p*-value adjustment by Holm method in case of Kruskal–Wallis test).

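### Stage 3: the four power figures for the planned one-way ANOVAs do not follow from d = 0.8 (0.73–0.80 against the stated 0.90–0.92), and one and the same test is given two different group sizes

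*Protocol article*

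**What the plan says.** The Stage 3 section on participants (Intervention) opens its sample size paragraph with "Cohen’s d effect size index of 0.8, correlations among repeated measures of 0.5"; alpha is 0.05. It then gives a size and a power for each outcome:

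- Correct answers: "results indicated that 18 participants in each group would be enough to provide an estimated power of 0.92 for group comparisons". For the session comparisons the figures are a size of 15 and a power of 0.90. Here d = 0.8 and alpha 0.05 are repeated in brackets, without the correlation.
- ASRS scores: "results indicated that 16 participants in each group would be enough to provide an estimated power of 0.92". The session comparisons are given a size of 18 and a power of 0.90.

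The enrolled size follows: "A total of 72 participants will take part to this Stage and will be divided in four groups", 18 in each.

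The tests are named in the Stage 3 data analysis sections. For ASRS, "Group comparisons will be conducted by one-way ANOVAs on T-scores for each assessment session and symptom domain"; sessions are compared by one-way ANOVAs within each group. The section on behavioral data plans the same two one-way ANOVAs for the number of correct answers, for each deviant separately. The outcome sections give five behavioral sessions (pre, mid, end, and 2 and 6 weeks after) and three ASRS sessions (pre, and 2 and 6 weeks after).

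**The concern.** Two things do not fit.

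1. **Two sizes for one test.** The group comparison of correct answers and the group comparison of ASRS scores are both a four-group one-way ANOVA at a single session. The stated effect, alpha and power are the same, yet one is said to need 18 per group and the other 16.

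2. **Powers too high for the stated effect.** For a four-group ANOVA with 16 to 18 per group and d = 0.8, a power of 0.92 looks too high, and the session figures raise the same doubt.

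These figures matter because 18 is the largest requirement in the paragraph and is exactly the size enrolled. A reader who meets a non-significant result would take it to come from a trial with about 92% power for d = 0.8. There is no margin either, although the Discussion warns that withdrawals may be frequent.

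**Working it through.** **Inputs.** From the Stage 3 sample size paragraph: d = 0.8, alpha 0.05, four groups, and the stated sizes and powers. From the analysis and outcome sections: one-way ANOVA throughout, k = 4 groups, k = 5 behavioral sessions, k = 3 ASRS sessions.

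**Formula.** Fixed-effects one-way ANOVA with k cells of n: noncentrality λ = f²·k·n, degrees of freedom k − 1 and k(n − 1), and power = P(noncentral F > F₀.₉₅).

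**From d to f (assumption).** G*Power's ANOVA needs f, and the article gives only d. I take f = d/2 = 0.40. This is the most favourable reading: no set of means spanning 0.8 SD gives a larger f. With equally spaced means the four powers below fall to 0.44–0.54.

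**Check on the article's own figures.**
- Stage 1, 19 words × 6 emotions: λ = 0.16 × 114 = 18.24, df 5 and 108, power 0.916 (stated 0.92). Reproduced.
- 34 per cell, if read as two cells: λ = 0.16 × 68 = 10.88, df 1 and 66, power 0.902 (stated 0.90). Reproduced.

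**The four Stage 3 figures at f = 0.40.**

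| Comparison | k × n | λ | df | Stated | Recomputed |
|---|---|---|---|---|---|
| Correct answers, groups | 4 × 18 | 11.52 | 3, 68 | 0.92 | 0.799 |
| Correct answers, sessions | 5 × 15 | 12.00 | 4, 70 | 0.90 | 0.771 |
| ASRS, groups | 4 × 16 | 10.24 | 3, 60 | 0.92 | 0.742 |
| ASRS, sessions | 3 × 18 | 8.64 | 2, 51 | 0.90 | 0.726 |

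The gaps are 12 to 18 percentage points, well beyond rounding.

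**Effect that the stated powers need.** f is about 0.47 for both correct-answer figures (d about 0.94) and about 0.50 for both ASRS figures (d about 1.0). At f = 0.50 the ASRS figures come out at 0.917 and 0.902.

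**Can 16 and 18 both be right?** At f = 0.50, 16 per group gives 0.917 but 18 gives 0.948. At f = 0.40 the pair is 0.742 and 0.799. At a common f the two sizes do not both round to 0.92.

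**Size that d = 0.8 would need at f = 0.40.** Four groups: 25 per group for 0.92. Five sessions: 21 for 0.90. Three sessions: 28 for 0.90.

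**Power at the enrolled 18 per group, f = 0.40.** Four groups, either outcome: 0.80. Five sessions: λ = 0.16 × 90 = 14.4, df 4 and 85, power 0.86. Three sessions: 0.73.

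**Group 1 against Group 2 under the planned Tukey test.** Four groups, 68 df: critical t = 2.634. Noncentrality d·√(n/2) = 0.8 × 3 = 2.4, power 0.41. Power 0.90 needs d of about 1.31.

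**The case against.** **The convention is inferred.** Cohen's d does not define f for more than two groups, and f = d/2 does not reproduce every one-way figure in the article. At d = 0.9 (f = 0.45), 22 words × 3 voices gives 0.902 (stated 0.91), and 17 words per level gives 0.947 if six voices are counted (stated 0.92). That stands: the recomputed values are conditional on f = d/2. It does not rescue the stated powers, because any other reading of a 0.8 SD span lowers them, and the 18-against-16 contradiction needs no convention.

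**Another test may have been entered.** The paragraph opens with a correlation of 0.5. A repeated-measures between-group calculation at f = 0.40 with 16 per group gives 0.905 with three measurements and 0.923 with four. A reader might infer from the match at f = 0.50 that a larger effect was typed in for ASRS. The article cannot settle whether the slip was in the effect size or in the choice of test. Neither explanation makes the figure apply to the planned one-way ANOVA. Treating sessions as a within-subject factor at correlation 0.5 gives 0.978 (5 sessions, n = 15) and 0.954 (3 sessions, n = 18), which also miss 0.90.

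**Not all of Stage 3 is affected.** A reader might conclude that every Stage 3 power is wrong. The ERP figures broadly follow from f = 0.40 and correlation 0.5: 11 per group over five sessions gives 0.905 (stated 0.91), and 13 per group gives 0.91–0.92 with about 20 or more repeated measures (stated 0.92). For reaction times between groups, 13 per group with six stimuli gives 0.875 against 0.91, a minor gap that does not set the enrolled size.

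**No pairwise power is claimed.** Groups 2 to 4 are all named as controls, so the lack of a figure for Group 1 against Group 2 is not an arithmetic error. This stands; such a figure is optional.

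**Conclusion.** The point holds for the four one-way ANOVA figures and for the two sizes given to one test. At d = 0.8 and alpha 0.05, the powers are 0.80, 0.77, 0.74 and 0.73, against the stated 0.92, 0.90, 0.92 and 0.90. This rests on f = d/2 = 0.40, equal group sizes and no dropout. The first two of these are favourable or as planned, and dropout would lower the figures further.

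The contradiction between 18 and 16 per group rests only on the stated inputs and the planned tests. At 18 per group the four-group omnibus test still has about 0.80 power, so the design is not shown to be unworkable. What is wrong is the stated justification for its size.

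**What to change.** Keep 18 per group and correct the Stage 3 sample size paragraph in one of two ways:

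- **Restate power at d = 0.8 (f = 0.40), n = 18:** 0.80 for four-group comparisons of both outcomes, 0.86 for sessions on correct answers, 0.73 for sessions on ASRS scores. State the conversion from d to f.
- **Or disclose what was entered.** If the one-way ANOVA was used, that means f of about 0.47 for correct answers and about 0.50 for ASRS scores, with a reason for each. If another test was used, name it and reconcile it with the planned analysis.

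Either way, give one size for the four-group one-way ANOVA, or explain why the two outcomes differ. If power for Group 1 against Group 2 is added, give it for the planned Tukey test: about 0.41 at d = 0.8, with 0.90 reached only at d of about 1.31.

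The cost is a few restated, less favourable numbers. Enrolment and the analysis stay as they are.

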## Discussion

This project of investigation aims to fulfill three main gaps of the current scientific literature. First, acoustic parameters from Castilian and Mexican Spanish will be analyzed in order to validate a newly formed emotion speech database for Mexican Spanish and to highlight cross-cultural differences in the way of expressing emotions by prosody. The first issue was to determine which acoustic features should be considered to optimize the distinction from one emotion to another. As no reliable set of acoustic features exists yet, a literature review of prosodic emotional speech parameters was conducted. MFCC coefficients were the most usually extracted features for machine learning applications. This analysis consists of computing the log values of a linear cosine transform of spectral parameters on a Mel scale, thus considering the human particularities of frequency responses (Caballero-Morales, 2013). Other recurrent spectral features were the pitch (fundamental frequency), formants, jitter, shimmer and harmonics-to-noise ratio (Swain et al., 2018). Formants are high-energy frequencies acoustic resonances of the vocal tract (Gelfand, 2009). They are generally labeled F1, F2, F3, and so on, from the lowest formant to the highest: the first three- formants are usually extracted for emotions discrimination (Kamińska, 2019). Jitter and shimmer refer to a period-to-period fluctuation of the pitch and the energy, respectively (Arruti et al., 2014). The harmonics-to-noise ratio considers the energy of the harmonics according to the one of other frequencies. It is directly correlated to the voice quality according to breathiness and roughness and is a principal component to characterize human voices (Arruti et al., 2014). The energy, intensity and rate were other features commonly used for emotional prosody recognition (Swain et al., 2018). Therefore, it is suitable to extract those acoustic parameters for the present work and predict high accuracy in emotions discrimination and classification. However, previous studies have also highlighted the influence of linguistic parameters on emotions processing (Méndez-Bértolo et al., 2011; Palazova et al., 2011; Hinojosa et al., 2014). Therefore, it is necessary to supervise linguistic values, for all stimuli to be nouns and adjectives, valence, arousal, and emotional category to be in accordance with prosody, and frequency, concreteness, and familiarity matched between emotions, so that the unbiased allocation of prosody during recordings may be ensured. Controlling for these factors will add reliability to our database and enrich the current available material, as previous works for Spanish emotional utterances did not systematically control for linguistic features (Caballero-Morales, 2013; Hinojosa et al., 2016a, b; Pérez-Espinosa et al., 2020).

The second aim of the present work is to determine the essence of the naturalness of human voices compared to synthesized ones by analyzing acoustic features. Previous studies have highlighted the human specific ability to recognize the human shape of human voices over synthesized ones (Tamura et al., 2015; Kuriki et al., 2016). For instance, Tamura et al. (2015) emphasized that human voices are generally perceived as more natural (as compared to awkward), human (as compared to robotic), animated, familiar, comfortable (as compared to irritating), emotional and warmer than artificial voices. Furthermore, the left posterior insula was outlined as a marker of the perception of the ecological validity with greater activation when processing human versus artificial voices. Therefore, by their highly natural identity, human voices may have a particular acoustic profile that allow their conspecific- and socially related neuronal processing and perception. To the best of our knowledge, the present work will be the first to detangle the acoustic identity of the human naturalness in voices compared to synthesized ones. Autistics have demonstrated impairments to associate human versus artificial voices with familiarity, warmth, emotions, animateness, naturalness (as compared to unnatural), and humanness (as compared to mechanics), and this atypical perception was correlated to the general autistic symptomatology (Kuriki et al., 2016). Therefore, ASD are characterized by impairments in the ability to discern social and human-related cues in human voices compared to synthesized ones, which invalidate them for further socio-emotional interactions. The present work proposes to reduce the human and natural-related acoustic information in voiced emotional utterances in order to create a more mechanistic and stereotyped environment which would be more comfortable and increase attention and interest to emotional stimuli in autistics. By gradually removing naturalness in voice, we pretend to identify up to which grade this process may help to improve emotional prosody discrimination in autistics. As a secondary outcome, it would be characterized how emotional processing preferences may vary according to human-likeness (Mori et al., 2012).

Finally, the present project of investigation seeks to explore the EEG event-related basis of emotional prosody uttered by human and synthesized voices processing in autism. Also, the emotions processing-related social robot-induced neuronal plasticity will be analyzed. Previous studies outlined significant plastic neuronal changes correlated to behavioral improvements after drug-free interventions in autistics, even in patients older than early critical plasticity periods. Particularly, Van Hecke et al. (2015) observed a significant alignment to typical neuronal resting activity highlighted by a shift from right to left hemisphere dominance of gamma oscillation activity after 14 sessions of the Program for the Education and Enrichment of Relational Skills in autistic adolescents (mean age = 14-year-old) which correlated to social abilities improvements. Using and ERP analysis before and after training for face processing, Faja et al. (2012) emphasized a post-training reduction of the amplitude of the P1 component in autistic adults (mean age = 22-year-old) stressing a potentially lower early attentional effort for face processing, in line with behavioral improvements. Nevertheless, no social robot-based intervention assessed pre- and post-electrophysiological correlates yet. Therefore, the present study suggests fulfilling this gap by highlighting the neuronal plasticity associated with the effects of a social robot-based intervention directed toward emotional prosodies discrimination skills. Behavioral improvements as measured by the ASRS questionnaire and responses to the experimental task are anticipated. Measuring behavioral outcomes by the validated ASRS questionnaire increases this work’s reliability and allows to extend results to daily life and human interactions as well as to improvements beyond (yet related to) the primary-trained skill (Yun et al., 2017; So et al., 2018; David et al., 2020). The enhancement of the intervention by synthesized voices and a social robot may lead to a multisensorial, real-life-like, safe, controllable, and simplified environment that may foster positive outcomes.

This project of investigation might encounter some pitfalls and unexpected results. Non-professionalism of actors recruited for emotional recordings during Stage 1 may affect the reliability of required prosodies. Nevertheless, the number of volunteers will be increased in order to generate four times more utterances than necessary to enable the selection of best actor participants. Furthermore, emotion recognition accuracy will be validated by supervised learning algorithm to ensure the quality of emotion discrimination based on acoustic features. Stage 2 aims to explore emotional recognition impairments in autism triggered by naturalness of human voices. We expect to observe a diminution of the amplitude of ERPs in the autistic population as a reflect of decreased attentional, sensorial, and cognitive emotional processing (Lartseva et al., 2015; Lindström et al., 2016, 2018). The autistic condition may also be characterized by hemispheric lateralization anomalies due to lateralized compensatory brain activity (Subbaraju et al., 2018). Impairments are expected to fade with the decreasing naturalness of voice stimuli. However, in the opposite case, no effect of naturalness on neural emotional processing by autistic children would be an evidence that the modulated acoustic parameters would not participate to autistic impairments. In the latter situation, or in case of enhancement of autistic impairments triggered by naturalness modulations, the acoustic edition of the stimuli will be reconsidered. Finally, Stage 3 expects the implementation of less natural voices in a robot-based intervention with the aim of improving emotion detection by autistic children. The 2-week intervention may imply a high rate of withdrawals whereas the sample size needed is relatively high. However, upon completion, we expect the intervention to trigger a reduction of autistic impairments (reduction of symptomatology, higher EEG activity, higher behavioral accuracy for emotion discrimination: smaller reaction times, and higher correct answers at end- and follow-up assessments).

